## Abstract

**Background:**

Taiwan has a high national caesarean rate coupled with a low vaginal birth after caesarean (VBAC) rate. This study aims to develop and evaluate a web-based decision-aid with communication support tools, to increase shared decision making (SDM) about birth after caesarean.

**Methods:**

A quantitative approach will be adopted using a randomized pre-test and post-test experimental design in a medical centre in northern Taiwan. The web-based decision aid consists of five sections. Section 1 provides a two-part video to introduce SDM and how to participate in SDM. Section 2 presents an overview of functions and features of the birth decision-aid. Section 3 presents relevant VBAC information, including definitions, benefits and risks, and an artificial intelligence (AI) calculator for rate and likelihood of VBAC success. Section 4 presents the information regarding elective repeat caesarean delivery (ERCD), involving definitions, benefits, and risks. Section 5 comprises four steps of decision making to meet women’s values and preferences. Pregnant women who have had one previous caesarean and are eligible for VBAC, will be recruited at 14–16 weeks. Participants will complete a baseline survey prior to random allocation to either the control group (usual care) or intervention group (usual care plus an AI-decision aid). A follow up survey at 35–38 weeks will measure change in decisional conflict, knowledge, birth mode preference, and decision-aid acceptability. Actual birth outcomes and satisfaction will be assessed one month after birth.

**Discussion:**

The innovative web-based decision-aid with support tools will help to promote pregnant women’s decision-making engagement and communication with their providers and improve opportunities for supportive communication about VBAC SDM in Taiwan. Linking web-based AI data analysis into the medical record will also be assessed for feasibility during implementation in clinical practice.

**Trial registration:**

ClinicalTrials.gov identifier (NCT05091944), Registered on October 24, 2021.

## Introduction

### Background and rationale {6a}

Elective repeat cesarean delivery (ERCD) contributes to a significant proportion of cesarean delivery (CD) rates in many high and middle-income countries [1–4]. Although CD is considered to be a relatively safe procedure, it has been associated with an increased risk of adverse maternal and neonatal outcomes [5, 6]. A recent scoping review showed that women are not adequately engaged in decision-making in relation to planned CD [7]. Vaginal birth after caesarean (VBAC) is a safe and reasonable alternative for most women who have experienced previous CD [8], yet many health professionals and health care organizations remain reluctant to offer VBAC, in part due to concerns about uterine rupture and perinatal death [9–12].

Shared decision making (SDM) is a patient-centered approach to promote collaboration between patients, family members, and healthcare providers as they navigate complex value-sensitive decisions together [7, 13–15]. SDM is the preferred approach for making healthcare decisions when more than one reasonable option is available [16]. Compared to the traditional paternalistic model of decision making, SDM emphasizes that the patient is actively involved in decision making, with information exchange and opportunity to express treatment preferences [17]. SDM is a process in which decisions are made in a collaborative way, where trustworthy evidence-based information is provided in accessible formats about a set of options, typically in situations where the concerns, personal circumstances, and contexts of patients, and their families play a major role in decisions [18]. There is a clear need for medicine to be more patient centered and for patients to be more actively involved in their care decisions [16]. Clinicians and patients need to work together to understand the patient’s situation, and to determine how best to address patient problems [16]. Effective communication is essential for achieving SDM [14, 16]. A three talk model of SDM involves choice talk, option talk and decision talk [18]. With further development, the three talk was modified into team talk, option talk and decision talk [18]. The revised three-talk model of SDM depicts conversational steps, initiated by providing support when introducing options, followed by strategies to compare and discuss trade-offs, before deliberation, based on informed preferences [18]. It is critical to develop an understanding of the human situation, to work together, to discuss and discern ways forward that make sense for each person in context [16]. Such humanistic practice is rooted in the recognition of the human meaning of care and in a concern for human emotions, source of suffering, and peace of mind [16]. Without empathy, the execution of the SDM process could be formally correct but ineffective in practice [16].

Taiwan has sustained a high national caesarean rate of over 35% for more than a decade [19]. Studies suggest that efforts to increase VBAC could be potentially important in reducing the high CD rates in Taiwan [20–22]. In 2003, the Bureau of National Health Insurance (NHI) used to propose a VBAC case payment to encourage physicians performing VBAC with the same case payment as CD in 2003. In 2005, NHI further proposed another policy of health insurance payment with the equivalent fees for a normal vaginal birth and CD [23–27]. However, the financial incentives, designed specifically for obstetricians, had limited effects on CD rates [24–26]. The prevalence of VBAC has remained less than 0.5% over two decades in Taiwan [19]. Several factors influence Taiwanese women’s decision making. Previous studies reveal that women have limited knowledge regarding birth choices after caesarean [28–30]. Lack of reliable information regarding the risks and benefits of VBAC resulted in women’s reluctance to attempt VBAC, due to fear of uterine rupture. Internet information, female friends, and family members were important sources of information and influential in women’s decision making about mode of birth [29, 31]. [name] et al. (2021) conducted a pilot study using an evidence-based decision-aid booklet to support women’s birth choices in Taiwan. Results demonstrated that using a birth choice decision-aid would be feasible to increase women’s knowledge, decrease decisional conflict and improve satisfaction [30]. However, despite these findings, the pilot study also revealed that many Taiwanese women were not prepared or expecting to participate in SDM with their obstetricians due to concerns about time constraints during consultations, and fear of asking questions [30].

### Objectives {7}

To redress gaps, developing a humanistic, women-centered decision support tool could potentially assist women, their families, and providers, to navigate value-laden birth decisions in Taiwan. Thus, this study aims to develop and evaluate a web-based decision-aid platform with communication tools to support women and providers in SDM about birth after cesarean in Taiwan.

### Trial design {8}

The Ottawa Decision Support Framework (ODSF) is utilized in the trial design [32]. Figure 1 outlines the larger multi-phase mixed methods study design sequence which the current study is nested into [17, 29, 30, 34]. The current study represents Aim 4 (Intervention implementing phase) (Fig. 1) and is a randomized control trial design. Stage 1 involves a randomized pre-test and post-test experimental design; decisional conflict, knowledge, birth mode preference, and decision-aid acceptability will be assessed. Stage 2 comprises a survey to measure actual birth outcome (VBAC or ERCD) and satisfaction.

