### Outcomes {12}

Primary outcome measures include decisional conflict (time frame: 14–16-weeks’ gestation and 35–38 weeks’ gestation), knowledge (time frame: 14–16-weeks’ gestation and 35–38 weeks’ gestation), birth mode preference (time frame: 14–16-weeks’ gestation and 35–38 weeks’ gestation), and decision-aid acceptability (time frame: 35–38-weeks’ gestation).Secondary outcome measures include actual birth outcome (time frame: one month after birth) and satisfaction with decision scale (SWD) (time frame: one month after birth).

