### Secondary outcome measures

#### Actual birth outcome

The principal researcher will ask women about their actual birth outcome one month after birth via Line App and verify this with the medical record.

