## Statistical methods

### Statistical methods for primary and secondary outcomes {20a}

Analysis will be by intention to treat. Data will be processed and analyzed using IBM SPSS version 28.0 software. Descriptive statistical analysis will include frequency, percentage, mean and standard deviation for each variable; chi-square test and Student’s t-test will be used to compare the differences between groups for the homogeneity of basic attributes. Statistical significance will be established using an α of 0.05. Bivariate analyses and linear regression models will be used to examine determinants of primary outcomes (decisional conflict score, knowledge score, birth mode preference), and secondary outcomes (mode of birth and satisfaction with decision). The strength of women’s birth mode preference will be analyzed using a non-parametric test (Wilcoxon signed-rank test).

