## Abbreviations

CD: Caesarean Delivery
ERCD: Elective Repeat Caesarean Delivery
VBAC: Vaginal Birth after Caesarean
SDM: Shared Decision Making

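### Mode of birth, a categorical secondary outcome, is assigned to linear regression, and its two stated labels leave no place for a caesarean after attempted VBAC

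*Protocol article*

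**What the plan says.** Three parts of the protocol article bear on this outcome.

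- **Definition.** Trial design {8}: "Stage 2 comprises a survey to measure actual birth outcome (VBAC or ERCD) and satisfaction". The abbreviation list expands the second label as "ERCD: Elective Repeat Caesarean Delivery". Outcomes {12} gives status and timing ("Secondary outcome measures include actual birth outcome (time frame: one month after birth") but no categories. The outcome measure section says that the principal researcher will "ask women about their actual birth outcome one month after birth via Line App and verify this with the medical record", again without categories.
- **Analysis.** Statistical methods {20a}: "Bivariate analyses and linear regression models will be used to examine determinants of primary outcomes". The same sentence carries the method on to "secondary outcomes (mode of birth and satisfaction with decision". Linear is the only regression named. The chi-square test appears in that section for another purpose: with the t-test, it is "used to compare the differences between groups for the homogeneity of basic attributes", that is, for baseline comparability.
- **Failed attempts are foreseen.** The intervention description {11a} includes a calculator that predicts each woman's chance of VBAC success, so the protocol accepts that some attempts will not succeed.

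The analysis is declared to be by intention to treat ({20a}), with complete-case handling of missing data ({20c}).

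**The concern.** There are two separate defects in one secondary outcome.

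**Model.** Mode of birth is a category, not a measured quantity. A linear model with covariates does not keep fitted probabilities between 0 and 1, and it imposes a constant change in probability per unit of covariate. Models described as examining determinants are covariate models, so this is where the choice does harm. A later analysis plan that used logistic regression would depart from the stated method.

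**Categories.** The intervention separates attempting VBAC from achieving it, but the outcome labels do not. A caesarean after attempted VBAC is neither a VBAC nor elective. If it is filed as ERCD, the trial reports an elective caesarean for a woman who had chosen otherwise. If it is left out, a randomised woman whose birth outcome is known disappears because of an event that the decision aid may make more or less frequent. The complete-case rule does not cover her, because her outcome is not missing.

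**Working it through.** **Inputs from the protocol.** Sample size {14}: effect size 0.50, α = 0.05, power 0.80, total 128, raised by 20% to 154. Allocation ratio is not stated; 1:1 is assumed. No attempt rate or success rate is given for eligible women or for the study site.

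**Step 1: the plan's own figure.** A two-sided, two-sample t-test with effect size 0.50 needs 63.77 women per arm, so 64 per arm and 2 × 64 = 128 in total (power 0.801). Then 128 × 1.2 = 153.6, rounded up to 154. Both figures reproduce. They were not derived for mode of birth; 128 is used below only as the number expected to be analysed.

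**Step 2: women without a category.** With attempt rate *a* and success rate *s*, the expected number is 128 × *a* × (1 − *s*). Both rates are assumptions.

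| Attempt rate | s = 60% | s = 70% | s = 80% |
|---|---|---|---|
| 10% | 5.1 | 3.8 | 2.6 |
| 30% | 15.4 | 11.5 | 7.7 |
| 50% | 25.6 | 19.2 | 12.8 |

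The range is 128 × 0.10 × 0.20 = 2.6 to 128 × 0.50 × 0.40 = 25.6, or about 3 to 26 women. If these women are filed as ERCD, the count of elective caesareans is too high by the same number.

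**Step 3: linear regression on a yes/no outcome.** Simulation with 64 women per arm, no true difference between arms, and one covariate with an assumed odds ratio of 2.5 per standard deviation; 2,000 datasets per row. The model was ordinary least squares on arm and covariate. Datasets with no VBAC were set aside (50% of them at a nominal rate of 0.5%, almost none elsewhere).

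| Nominal VBAC rate | Datasets with any fitted value outside 0–1 | Mean share of women outside 0–1 | Type I error, arm term |
|---|---|---|---|
| 0.5% | 96% | 25% | 0 |
| 5% | 93% | 14% | 0.036 |
| 10% | 95% | 11% | 0.044 |
| 20% | 97% | 7% | 0.0515 |
| 30% | 93% | 5% | 0.0525 |

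Impossible fitted values appear at every rate tried, so this part does not depend on VBAC being rare. The test of the arm term is close to its nominal level at rates of 5% or more.

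**The case against.** **The coding is inferred.** The two labels stand in a design overview, the sections that define the outcome list no categories, and the data form is not shown. A caesarean in labour would be visible in the medical record. This stands as a limit: the protocol does not say that such women will be misfiled or dropped. It does describe the outcome in two labels that cannot hold them, and no other section adds a third.

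**The linear model may be harmless for comparing arms.** Without covariates, its arm coefficient is the risk difference, which is also the measure recommended here, and the planned bivariate analyses could include a cross-tabulation by arm. This stands, and it confines the model defect to adjusted analyses. A reader might infer that standard errors for the treatment comparison are generally unreliable; Step 3 does not support that at rates of 5% or more.

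**Loss of power and a hidden effect.** A reader might infer that the two labels cost power. For example, with attempts of 40% versus 20% and 70% success, VBAC is 28% versus 14%, and power at 77 per arm goes from about 78% to about 58%. Those figures compare two different endpoints, attempted and achieved VBAC. Filing failed attempts as ERCD leaves the VBAC count at 28% versus 14%. Dropping them gives 28/88 = 31.8% versus 14/94 = 14.9%, a wider gap on a biased denominator. Nor is the effect on choice hidden: birth mode preference at 35–38 weeks is a primary outcome, and women confirm their preferred mode with the obstetrician before that survey.

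**Rarity.** A reader might take "The prevalence of VBAC has remained less than 0.5% over two decades in Taiwan" to mean that VBAC will be rare in this trial. That figure is national and has no stated denominator, and no rate is given for eligible women at this site. It would also conflict with assumed attempt rates of tens of percent.

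**Conclusion.** The point holds in a limited form, for a secondary outcome.

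- **Firm, from the text:** mode of birth is assigned to linear regression, no categorical model is named, and the two stated labels exclude a caesarean after attempted VBAC.
- **Size of the category gap:** about 3 to 26 of 128 women, resting wholly on assumed attempt rates of 10–50% and success rates of 60–80%.
- **Size of the model problem:** fitted values outside 0–1 in 93–97% of simulated datasets with at least one VBAC, for 5–25% of women on average. This depends on the assumed covariate effect and applies to adjusted models only.

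The documents do not support a claim of lost power, of a hidden effect on choice, or of VBAC being rare at this site.

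**What to change.** **Statistical methods {20a}.** Remove mode of birth from the outcomes for linear regression. State that arms will be compared by risk difference with a 95% confidence interval over all randomised women with birth data, and that adjusted analyses will use logistic regression, penalised if events are few.

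**Trial design {8} and the actual birth outcome measure.** Replace the two labels by two recorded items, both taken from the medical-record check already planned:

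1. attempted mode (VBAC attempted or not);
2. final mode (VBAC, caesarean after attempted VBAC, repeat caesarean without an attempt).

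The cost is one extra field at the chart check and a change of wording. Sample size, primary outcomes and visit schedule stay as they are.

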**Fig. 1 Fig1:**
[figure not shown]
Study design

## Methods: Participants, interventions and outcomes

### Study setting {9}

The study will be conducted in a medical center in northern Taiwan, with 1300 annual births and a CS rate of 29.71%. The medical center offers a 24-h system of designated obstetric coverage. 
https://www.vghtpe.gov.tw/Index.action.

### Eligibility criteria {10}

Using purposive sampling, the selection criteria includes women aged between 20 and 45; have experienced one previous CD; 14–16 weeks’ gestation with at least a half year interval between current pregnancy and the previous birth; and are fluent in English or Mandarin. Exclusion criteria includes women with multiple pregnancy, previous classic CD, or myomectomy, and/or pregnancy with high risk of complications (for example, women who had risk factors such as hypertension, heart disease, diabetes, epilepsy, threatened premature labor, or another preexisting medical problem).

### Who will take informed consent? {26a}

The principal researcher [name] will invite eligible women to participate in the study. Prior to the study commencement, the participants will give written informed consent for participation after the principal researcher explain the purpose and procedure of the study.

### Additional consent provisions for collection and use of participant data and biological specimens {26b}

This trial does not involve collecting biological specimens.

### Interventions

#### Explanation for the choice of comparators {6b}

The control group condition is essentially ‘usual care’ and will enable comparison with the experimental condition in regard to the shared decision making intervention only, thereby minimizing the potential impact of any additional variables in the experiment. A maternal health booklet, produced by Health Promotion Administration, Ministry of Health and Welfare, Executive Yuan, Taiwan, will be provided to all women in the study [35]. The 58-page booklet is routinely provided to all women during pregnancy in Taiwan and includes Five (5) “Dos” and “Do nots” during pregnancy. Five (5) “Dos” content includes (1) Do receive prenatal exams according to schedule; (2) Do take good care during pregnancy; (3) Do recognize pregnancy complications; (4) Do know the signs of premature birth; (5) Do know the signs of labor. Five (5) “Do nots” content includes (1) Do not smoke or drink; (2) Do not be exposed to secondhand smoke; (3) Do not take medication without doctor’s orders; (4) Do not choose a C-section to pick the time of birth; (5) Do not use drugs [35]. There is very limited information relevant to mode of birth choice after caesarean.

### Intervention description {11a}

Women in the intervention group will receive both usual care plus access to the web-based decision-aid and access to on-line support. The web-based decision-aid platform was adapted from the original Birth Choices decision-aid by Shorten et al. [36, 37]. We invited 10 experts to evaluate the decision-aid platform for use in Taiwan, including five clinicians (two obstetricians, one head nurse and two supervisor), three midwives, and two academic professors. They provide feedback after consultation; the content validity was 0.97. The web-based decision-aid consists of five sections (Fig. 2). Based on the previous pilot study findings [35], we developed the platform to ensure women complete section and corresponding steps in sequence rather than skipping decision steps. Section 1 provides a two-part video, consisting of two 10-min segments. Part 1 introduces SDM, addressing how to prepare and participate in the study, and how to communicate with the obstetric provider using three talks (team talk, option talk and decision talk). Part 2 provides information with examples to practice communication skills using a BRAIN framework (benefits, risks, alternatives, intuition, and nothing) decision for a better birth plan [38]. Section 2 presents an overview of functions and features of the birth decision-aid. Section 3 presents relevant VBAC information, including definitions, benefits and risks, and an AI calculator for rate and likelihood of VBAC success [20, 33]. In this section the medical history data for pregnant women using the decision-aid platform will be retrieved from the hospital data Health Information System (HIS) system and transferred securely to the warehouse database through the local server. Simultaneously, using the AI model, the pregnant women’s clinical characteristics entered from the Web page will be integrated, cleaned, and converted into a format that will be used by AI edge computing to predict a personal success rate for vaginal birth. Finally, the results are returned to the database and displayed on the Web page through the RESTful API for the clinical staff to access. Section 4 presents the information regarding ERCD, involving definitions, benefits, and risks. Section 5 comprises four steps of decision making to meet women’s values and preferences. Step 1 consists of an animation, reviewing the benefits and risks of VBAC and ERCD. Step 2 consists of a 12-question quiz designed to measure knowledge about VBAC and ERCD. Step 3 presents 12 values clarification statements (6 for VBAC and 6 for ERCD). Using a 6-point Likert scale for each statement, women will be asked to respond to the question ‘what is important for you’, from very important (6 points) to do not consider (1 point). A score in accordance with women’s values for each option will be calculated immediately. Step 4 is designed to confirm women’s birth mode decision based on the values clarification exercise. The principal researcher will offer 2–3 individual online consultations via Line App to answer questions about the decision-aid and clarify information within the decision-aid. Women will be directed back to their provider for questions specific to their pregnancy and decision making.

**Fig. 2 Fig2:**
[figure not shown]
Web-based decision-aid platform

### Criteria for discontinuing or modifying allocated interventions {11b}

During the trial, if the intervention group participants experience any emergent situation such as vaginal bleeding, foetal heartbeat complications etc., we will inform them of their allocation to the intervention and allow them to decide whether continue to participate in the study.

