### Relevant concomitant care permitted or prohibited during the trial {11d}

Since there is no invasive intervention involved in this study, there will be no physiological risks involved in this study. Thus, no concomitant care and interventions are prohibited. The only psychological risk is the emotional distress that may arise from the sensitive questions asked during the counseling process. This study will provide personal assistance or referral to the relevant counseling department or support groups.

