### Procedure for unblinding if needed {17b}

During the trial, if the intervention group participants occur any emergent situation such as vaginal bleeding, fetal heartbeat complication etc., we will inform them and allow them to decide whether continue to participate in the study.

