### Plans to promote participant retention and complete follow-up {18b}

Reminders will be sent to participants through the Line app to complete questionnaire at three scheduled times (14–16-weeks’ gestation and 35–38 weeks’ gestation and one month after birth). Eligible participants will receive up to $300 Taiwanese (NTD) compensation for participating one month after birth. The research team will have weekly meetings to monitor the adherence and retention of participants.

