### Methods in analysis to handle protocol non-adherence and any statistical methods to handle missing data {20c}

Intention to treat analysis will be used and complete case analysis will be managed for missing data. We will undertake analysis to determine any systematic differences between those who do not adhere to the protocol or who drop out of the study.

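### The event-triggered choice offered only to intervention women covers leaving the study, not just stopping the decision aid: a small, avoidable risk of arm-dependent loss from the 35–38 week outcomes.

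*Protocol article*

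**What the plan says.** Under the discontinuation criteria {11b}, the protocol article states that "if the intervention group participants experience any emergent situation such as vaginal bleeding, foetal heartbeat complications etc., we will inform them of their allocation". The same sentence then leaves it to the woman whether she stays in the study. The unblinding procedure {17b} gives the same rule, again for the intervention group only, and says the team will "allow them to decide whether continue to participate in the study". Neither section describes a corresponding contact for control women with bleeding or a foetal heartbeat problem.

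On risk, the concomitant care section {11d} says "there will be no physiological risks involved in this study". It goes on to name one psychological risk, distress caused by sensitive questions during counselling, and offers help or referral for it.

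On analysis, section {20a} says "Analysis will be by intention to treat". Section {20c} adds that "complete case analysis will be managed for missing data" and promises a check for "any systematic differences between those who do not adhere to the protocol or who drop out of the study". Section {18b} provides for "weekly meetings to monitor the adherence and retention of participants". For actual birth outcome, the researcher will ask the woman and "verify this with the medical record".

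**The concern.** Bleeding and foetal heartbeat problems should arise about equally often in the two randomised groups. What differs is the response. An intervention woman is contacted and offered a decision about the study; no such contact is described for a control woman. The rule operates between baseline at 14–16 weeks and the survey at 35–38 weeks that supplies decisional conflict, knowledge, birth mode preference and acceptability.

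Stopping a decision aid and leaving follow-up are different acts. A woman who stops the aid can still answer the surveys and be analysed in her allocated group. A woman who leaves the study cannot. Because the wording merges the two, some women who only want to be rid of the platform may be lost altogether. Under complete-case analysis they then drop out of the comparison, in one arm, for a reason linked to an obstetric event. Intention to treat fixes the group in which a woman is counted, but it cannot supply an answer that was never collected.

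**Working it through.** **1. The texts side by side.** The heading of {11b} concerns stopping or changing the allocated intervention; its sentence offers a choice about the study. The heading of {17b} concerns unblinding; its sentence offers the same choice. Intervention women already hold a username and password for the platform (Participant timeline {13}), so being told their allocation adds little. The practical content of the rule is the choice about staying.

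**2. The plan's own sample size.** Inputs from Sample size {14}: effect size 0.50, α = 0.05 (two-sided assumed; not stated), power 0.80. A two-sample t-test with 64 per arm has power 0.801, which reproduces the total of 128. The inflated total is 128 × 1.20 = 153.6, rounded up to 154, or 77 per arm if allocation is 1:1 (assumed).

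**3. Size of a possible shift.** The article gives no event rate, exit rate or outcome difference. All three are assumed here:
- e = share of women with an emergent event, the same in both arms
- w1, w0 = share of those women who leave, in the intervention and control arm
- d = outcome difference, in SD, between women with and without an event

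In one arm the full mean lies d·e above that of event-free women. Among completers it lies d·e(1 − w)/(1 − e·w) above. The difference between these is d·e(1 − e)·w/(1 − e·w). The net shift between arms is therefore

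d·e(1 − e)·[w1/(1 − e·w1) − w0/(1 − e·w0)],

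and expected exits per arm are 77·e·w.

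| e | w1 | d | w0 | Exits, intervention / control | Net shift (SD) | Share of 0.50 |
|---|---|---|---|---|---|---|
| 0.05 | 0.25 | 0.3 | 0 | 0.96 / 0 | 0.0036 | 0.7% |
| 0.05 | 0.25 | 0.3 | 0.125 | 0.96 / 0.48 | 0.0018 | 0.4% |
| 0.10 | 0.50 | 0.5 | 0 | 3.85 / 0 | 0.0237 | 4.7% |
| 0.10 | 0.50 | 0.5 | 0.25 | 3.85 / 1.93 | 0.0121 | 2.4% |
| 0.10 | 0.50 | 0.5 | 0.50 | 3.85 / 3.85 | 0 | 0% |

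Worked example, third row: 0.5 × 0.10 × 0.90 × (0.50/0.95) = 0.045 × 0.526 = 0.0237.

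**4. Against sampling error.** With 64 per arm the standard error of the difference is √(2/64) = 0.177 SD. The largest shift in the table is 0.0237/0.177 = 0.13 of a standard error.

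**5. Power.** With 64 control completers, losing 2 or 4 further intervention women from 64 lowers power from 0.801 to 0.795 or 0.788.

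**The case against.** The strongest reply is that the one-arm wording follows from the headings. Section {11b} asks about stopping the allocated intervention, and control women have none to stop. On that view the reference to the study is loose wording for the aid, and no differential exit from the surveys is intended. This explains why one arm is named. It does not explain why the choice reaches follow-up, and staff applying the text as written would be offering exit from the study.

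A reader might also infer that the article gives no safety reason for a one-arm contact, because it denies any physiological risk. That goes too far. The sentences that follow in {11d} name distress from counselling, and the online consultations are described for intervention women only. A check-in with a woman who is bleeding while receiving that contact is reasonable. What it justifies is a pause or stop of the consultations; it does not require her to leave the surveys.

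Third, the text allows a decision and does not encourage leaving. The consent form, which is not shown, may tell every woman that she can withdraw. Both points are fair, and control women may indeed leave after such events, which would offset the effect. The finding rests on what the two sections state, not on what a condensed article leaves out.

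Finally, safeguards exist. High-risk pregnancies are excluded at entry, retention is reviewed weekly, dropouts are to be compared, birth mode can be checked in the record, and the sample size carries a 20% allowance. Some women with serious events will deliver before 35 weeks and miss the survey in either arm. These points limit the harm. But the dropout comparison detects loss without preventing it, the allowance protects power and not against bias, and the record does not hold the survey outcomes.

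**Conclusion.** The point holds as a minor one. Two sections tie an event-triggered choice, in one arm, to participation in the study, and complete-case analysis turns any resulting exit into a missing primary outcome. The likely effect is small: about 1 to 4 of 77 intervention women, and a shift of about 0.004 to 0.024 SD if no control women leave, roughly halved if control women leave half as often, and zero if they leave equally often. Every rate behind these figures is assumed; only the sample size comes from the article.

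Two stronger readings are not supported. A reader might infer that the bias favours the aid, for example on birth mode preference, because women with complications would be missing from the intervention arm. Nothing in the article shows how such women would score on any outcome, so the direction is unknown. A reader might also infer a material bias. A shift of 0.075 SD needs events in 15% of women, every one of them leaving, none leaving in the control arm, and a 0.5 SD difference (0.5 × 0.15 = 0.075). The article offers no basis for that combination.

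**What to change.** Reword {11b} and {17b} so that the choice after an emergent event is whether to stop using the decision aid and the online consultations. State that women who stop remain in the 35–38 week and postnatal surveys and in the record-based collection of birth outcome, unless they withdraw consent for data. Report such events, and exits after them, by arm. The check-in itself can stay.

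The cost is a wording amendment and a simple log of events and exits in both arms. The sample size does not change, and the extra loss attributable to this rule falls to zero.
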